**Fig. 3 Fig3:**
[figure not shown]
Standard Protocol Items: Recommendations for Interventional Trials (SPIRIT) Figure. *PFMGT* pelvic-floor-muscle group therapy

The PFMT protocol has been published previously by Bø et al. [31], and is based on the Norwegian Aerobic Fitness Model. It follows the general training principles and the recommendations concerning physical activity practice during and after pregnancy according to the American College of Obstetricians and Gynecologists and the World Health Organisation (WHO) [31, 32] (Table 1).

**Table 1 Tab1:** Types of training provided during MOTHERFIT1 and MOTHERFIT2 with accompanying aim and exercises

Type of training	Aim	Exercise(s)
Awareness	Continue breathing during PFM contraction	Breathing and PFM exercises
Skills	Consciously timed voluntary pre-contraction	The ‘Knack’– closing of vaginal hiatus and in-, up- and forward movement of the PFMs before and during increased abdominal pressure
Functional	Increase awareness to avoid unnecessary abdominal pressure and to prevent unnecessary or extreme perineal descent during daily activities	Correct pushing technique during defecation, or a PFM contraction in situations associated with a rise in abdominal pressure
Muscle strength and endurance	Build up long-lasting muscle volume, providing structural support/‘stiffness’, resulting in reduced perineal descent	Slow velocity • Build up to 8–12 contractions, of 6–8 s (if possible), add 3–4 fast contractions on top at the end to recruit more slow-twitch fibres. Start with double time rest (complete relaxation) between contractions • Three sets of exercises during the day in varying positions: lying, sitting, kneeling, standing position • Preferably daily training, but minimally 3–4 days a week, during at least 5–6 months • Maintenance muscle strength after 6 months’ training; 2 days a week where intensity is more important than frequency
Muscle contraction: speed	Build up explosive strength	Fast repetitions • Build up from 10 sets of 3 quick contractions to 10 sets of 5 quick contractions, 3 times a day

*PFM* pelvic-floor-muscle training

Moreover, all women receive a mApp (iPelvis) [33], an application with individualised pelvic physiotherapy exercises, and supportive video content and images. Performance and adherence to PFMT will be recorded in the participants’ personal training diary and is reinforced by the regularly sending of push notifications on the mApp. The training diary will be available for the motherfit group therapists and may be used to discuss the participants’ motivation to incorporate adequate PFMT and use of PFM in their daily activities. Although adverse events due to PFMT are very rare [20], adverse event forms are used to register their occurrence during the motherfit group therapy.

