The primary objective of this study is to investigate whether a structured assessment and treatment programme (motherfit group therapy) of intensive, supervised PFMGT, including a home maintenance programme, reduces 18 months’ post-partum UI severity (frequency, amount and impact) compared to CAU in adult pregnant women (MOTHERFIT1) and post-partum women with SUI (MOTHERFIT2). The secondary objective is to investigate whether motherfit group therapy is cost-effective compared to CAU in pregnant (MOTHERFIT1) and post-partum women with SUI (MOTHERFIT2) 18 months post-partum.

It is hypothesised that intensive, supervised, pre-partum (study 1: MOTHERFIT1) or post-partum (study 2: MOTHERFIT2) PFMGT is more (cost-)effective compared to CAU in adult pregnant (MOTHERFIT1) or post-partum women with SUI (MOTHERFIT2).

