### Participants

Women will be included if they meet all of the following criteria: (1) aged ≥ 18 years, (2) UI (stress or mixed with predominant stress UI factor, according to Haylen et al. [6], (3) a score of > 3 on the International Consultation on Incontinence Modular Questionnaire-Urinary Incontinence-Short Form (ICIQ-UI-SF) questionnaire [27], (4) are motivated for participation in the motherfit programme, (5) are competent to speak and understand the Dutch language and to read and fill in forms independently and (6) have a mobile app (mApp) on a tablet (Apple or Android) available.

Exclusion criteria are: (1) UI prior to first pregnancy, still existing during pregnancy, (2) high-risk pregnancy, resulting in a contra-indication for performing intensive pelvic-floor-muscle (PFM) exercises (e.g. placenta praevia, vaginal blood loss, preterm uterine contractions), (3) suffering from significant exercise limitations or co-morbidities (physical or psychological) that would restrain a woman from participation in motherfit group therapy, (4) a history of chronic neurological disorders or diseases related to UI (e.g. multiple sclerosis, cerebrovascular accident, diabetes mellitus (during ≥ 1 year with glycated hemoglobin (HbA1c) > 10 mmol/l)), (5) urinary tract infection (urine-sediment, urine culture), (6) a history of anti-incontinence or urogynaecological surgery, (7) women who are expected to be lost to follow-up (e.g. because of a planned change of residency), (8) have had recent pelvic physiotherapy (< 6 months) and (9) refusal to use a mApp.

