### Interventions

#### Care-as-usual

In case participants with SUI are allocated to the CAU group, participating case managers give their normal advice and women make their own choices as to whether they want to participate in any kind of pregnancy-related course, visit to a physician or therapist.

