#### Motherfit group therapy

All women allocated to motherfit group therapy, and unaware or unable to contract their PFMs correctly, will be referred to the PPT for individual instruction before joining the motherfit group therapy (Fig. 3). Every participating region has a PPT who provides individual or group therapy. Motherfit consists of eight group therapy sessions of 60 min each, instructed and supervised by a registered PPT. In each group a maximum of four women are allowed to participate. Women of both studies can start when they have been randomised to motherfit group therapy. Therefore, the participant’s group composition may change over time. Motherfit includes instructions on pelvic floor anatomy and how to contract, relax and train the PFMs correctly and is combined with general physical exercises with a strong focus on self-management.

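### Adverse event forms are described only for the motherfit arm and for events attributed to the training, over an unclear time window, so as described they allow no between-arm comparison of harms

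*Protocol article*

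**What the plan says.** All of the following is from the protocol article.

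- **Interventions, Motherfit group therapy (text after Table 1).** The sentence on harms opens "Although adverse events due to PFMT are very rare" and ends "adverse event forms are used to register their occurrence during the motherfit group therapy". This is the only adverse event instrument described.
- **Interventions, Care-as-usual.** For the control arm, "participating case managers give their normal advice and women make their own choices as to whether they want to participate" in courses or visit a physician or therapist. No event form is mentioned.
- **Background, primary objective.** The intervention is "a structured assessment and treatment programme (motherfit group therapy) of intensive, supervised PFMGT, including a home maintenance programme".
- **Interventions, Motherfit group therapy.** "Motherfit consists of eight group therapy sessions of 60 min each, instructed and supervised by a registered PPT".
- **Table 1, muscle strength and endurance.** "Preferably daily training, but minimally 3–4 days a week, during at least 5–6 months".
- **Participants.** The examples given of a high-risk pregnancy that rules out intensive exercise are "placenta praevia, vaginal blood loss, preterm uterine contractions".
- **Blinding.** Participants, pelvic physiotherapists and, during the trial, the coordinating researcher are not blinded.
- **Data collection.** Follow-up is at 34 weeks of gestation, 6 weeks, 6 months and 18 months post-partum in MOTHERFIT1, and at 4, 9 and 18 months post-partum in MOTHERFIT2. Case managers also receive a survey on delivery two weeks after delivery.
- **Withdrawal of individual subjects.** All enrolled women are to be accounted for. Blood loss, premature rupture of membranes and pre-eclampsia are among the reasons a woman may be withdrawn.

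**The concern.** Some events that matter for an exercise programme in pregnancy also happen without exercise. The article's own exclusion and withdrawal lists name bleeding, and the exclusion list names preterm contractions. A count from one arm cannot separate this background from an effect of training.

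The wording adds a second restriction. The forms register events due to the training, so causality is decided before an event is counted, in a trial where the women and therapists know the allocation.

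The Discussion says implementation in peri-partum care and future guidelines should be considered if motherfit proves (cost-)effective. A reader of the results would then want to know whether harms differed between arms. The forms as described cannot answer that.

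**Working it through.** The plan states no figure on harms, so there is none to reproduce. The check is a reading of every place that could supply event data, followed by a calculation of what two-arm recording could show.

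**1. Which sources cover which arm**

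| Source | Arm | What it can give |
|---|---|---|
| Adverse event form | Motherfit | Events attributed to training |
| Weekly training diary | Motherfit | Exercise and activity; no event item described |
| Delivery survey | Not restricted by arm | One contact two weeks after delivery; items not listed |
| Withdrawal reasons | Both | Only events that end participation |

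In MOTHERFIT2 women are recruited at the six-week post-partum visit, so delivery precedes the intervention and delivery data cannot reflect it. No source described is a systematic event count in both arms.

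**2. Time window**

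The methods describe motherfit as eight sessions, while the objective includes home maintenance in the same term. The text gives no session spacing. If sessions were weekly or fortnightly (an assumption), supervision would last about 8 or 16 weeks. Table 1 asks for at least 5 to 6 months of training: 5 × 52/12 = 21.7 weeks to 26 weeks. On the narrow reading, part of the home-training period falls outside the window; on the broad reading it is inside. The article does not settle which applies.

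**3. Precision of a count within one arm**

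If no events are seen in n women, the one-sided 95% upper limit for the true rate is 1 − 0.05^(1/n).

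- MOTHERFIT1, n = 75: 3.9%.
- MOTHERFIT2, n = 45: 6.4%.
- After the planned 20% dropout, n = 75 × 0.8 = 60 gives 4.9%, and n = 45 × 0.8 = 36 gives 8.0%.

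**4. Power if both arms recorded events identically**

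The documents give no event rates, so those below are assumptions. Two-sided α = 0.05, with p̄ the mean of the two rates:

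power = Φ{[|p1 − p0| − 1.96·√(2p̄(1 − p̄)/n)] / √([p0(1 − p0) + p1(1 − p1)]/n)}

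Example, n = 75, 5% versus 10%: (0.05 − 1.96 × 0.0430)/0.0428 = −0.80, so power is 0.21.

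| Assumed rates | n = 75 per arm | n = 45 per arm |
|---|---|---|
| 5% vs 10% | 21% | 14% |
| 2% vs 10% | 54% | 36% |
| 5% vs 20% | 80% | 58% |
| 10% vs 30% | 87% | 67% |

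Two-arm recording would make a comparison possible, but only large differences would be detectable.

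**5. Recall**

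The longest gap between contacts is 18 − 6 = 12 months in MOTHERFIT1 and 18 − 9 = 9 months in MOTHERFIT2.

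**The case against.** The strongest reply is that this is a condensed article. Detailed safety procedures are commonly left to the full protocol, which is not shown; part of the article was also removed before review, and the figures and checklist are not visible. Silence about CAU does not show that CAU events go uncollected. This stands, and it limits the point to the method as described.

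A second reply is that the form's scope is coherent: it monitors harms of a programme while that programme is delivered, and the trials set no comparative safety outcome. That is fair as far as it goes. It explains why the form exists but does not make it informative about differences between arms.

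A third is that two-arm recording would have little power. The figures above bear this out, but counts by arm with intervals can still be interpreted as a comparison, which a one-arm count cannot.

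Some stronger readings are tempting, and the article does not support them:

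- *Events during home training are missed.* The text does not restrict the form to sessions, and the objective puts home maintenance inside motherfit group therapy. The window is ambiguous; it is not shown to be too short.
- *CAU events are recorded as none, so motherfit looks worse by construction.* Not collected is different from zero, and no between-arm table of harms is planned.
- *Nothing can be learned about exercise in pregnancy.* The delivery survey is not limited to one arm and withdrawal reasons cover both, so there is partial information. Exercise in pregnancy also concerns MOTHERFIT1 only.

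**Conclusion.** The point holds in a limited form. As described, event forms belong to the motherfit arm, target events already attributed to training, and have an unclear time window, so they permit no between-arm comparison of harms in either trial. The delivery survey and withdrawal reasons only partly fill the gap.

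No bias can be quantified, because the documents give no event rates and plan no harms comparison. The benefit of changing is real but modest: at 75 and 45 women per arm, only large differences could be detected under the rates assumed above. The conclusion rests on the article alone and falls away if the full protocol already collects events in the same way in both arms. The primary efficacy analysis is unaffected, so this is a worthwhile improvement and not a threat to the main result.

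**What to change.** 1. Add a short set of identical event items to the follow-up questionnaires that both arms already complete. Ask whether an event occurred, without asking whether training caused it.
2. Use pregnancy-specific items, such as bleeding and contractions, only at the pregnancy and early post-partum contacts of MOTHERFIT1 (34 weeks of gestation and 6 weeks post-partum). Use general items at the other contacts and in MOTHERFIT2.
3. Report counts by arm with confidence intervals, separately for each trial.
4. Keep the existing adverse event form, state that it covers the home-training period, and report it separately as an intervention-arm source.

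If the full protocol already provides for collection in CAU, a sentence saying so, together with the window in item 4, is enough.

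The costs are an amendment to the forms, a small respondent burden, recall of up to about 12 months at the last contact, and precision sufficient only for large differences. Items added after recruitment began would also be missing for contacts already completed.

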### Data collection and outcome measures

All data (electronic case report forms and questionnaires at baseline and follow-up) of the participants and case managers will be collected in a (web-based) digital central database. Demographic variables and personal characteristics will be registered by the Nederlandse Vereniging voor Obstetrie & Gynaecologie vragenlijst (NVOG-q) at baseline for MOTHERFIT1 and MOTHERFIT2.

MOTHERFIT1: data will be collected at baseline, 34 weeks of gestation, 6 weeks and 6 and 18 months post-partum.

MOTHERFIT2: data will be collected at baseline and 4, 9 and 18 months post-partum.

The case manager fills in a first survey after the inclusion of a participant. For MOTHERFIT1 these questions include, among others, expected delivery date and current medication use. Two weeks after delivery, case managers receive a second survey regarding delivery variables. For MOTHERFIT2 the case manager fills in identical surveys, except the question on expected delivery date.

Participants in the intervention group fill in a training diary and three questions regarding their general physical activity level, weekly. The PPTs will register attendance of the participant during the intervention period and send it by postal mail to the researcher.

### Primary outcome measure

Tables 1 and 2 show the schedule of assessments for MOTHERFIT1 and MOTHERFIT2. The primary outcome measure is self-reported UI based on the severity sum score of the ICIQ-UI-SF. The ICIQ-UI-SF is a brief (four questions) and robust measure for evaluating the frequency of symptoms and impact of UI [34]. The total score ranges from 0 (not affected) to 21 (severely affected). The ICIQ-UI-SF is divided into the following four severity categories: slight (1–5), moderate (6–12), severe (13–18) and very severe (19–21) [35]. The questionnaire is translated in Dutch [36]. Therapy success is defined as absence of UI or change from baseline of at least 3 points on the ICIQ-UI-SF at 18 months post-partum [37].

### Secondary outcome measures

Patient-reported improvement: the Patient Global Impression of Severity (GPE) questionnaire assesses patients’ self-reported improvement [38]. It is an accepted and reliable scale for incontinence, consisting of one question and seven response options [39, 40].

Quality of life outcomes: the Incontinence Impact Questionnaire-7 (IIQ-7) contains seven items that reliably assess the impact of UI on health-related quality of life (HRQL) [41, 42]. It determines UI impact on four domains: mobility, physical functioning, emotional health and embarrassment and ranges from 0 to 100.

General activity level: the diary has to be filled in weekly. Next to a question regarding the number of days PFM exercises have been executed, it contains three questions regarding general activity level. The questions on general activity level are modified from the Dutch healthy exercise norm (Nederlandse Norm Gezond Bewegen). This norm is based on publications of the American College of Sports Medicine [43].

### Adherence to home training programme

Only participants in the intervention group register their performance of requested pelvic-floor-muscle exercises, including their general physical activity, weekly, at home in the training diary. The training diary is a data entry form and, if scanned, an Excel file will be computer generated.

### Cost-effectiveness

For the purpose of the economic evaluation, a study-specific cost questionnaire has been developed. Participants’ resource use ((in) direct costs related to SUI) is collected from the societal and health care perspective. Furthermore, the EuroQol instrument (EQ-5D-5 L) will be administered, a validated, generic health-state measure [43, 44] widely used in economic evaluations. The five-level version (EQ-5D-5 L) is proposed by the recently updated Dutch guideline for economic evaluations in health care [45] and consists of the EQ Visual Analogue Scale and a descriptive system. The descriptive system comprises five dimensions: mobility, self-care, usual activities, pain/discomfort and anxiety/depression. Each dimension can be rated at five levels: no problems, slight problems, moderate problems, severe problems and extreme problems.

### Process evaluation

A study-specific questionnaire has been developed to evaluate patient satisfaction of motherfit group therapy (part 1, 10 items) and satisfaction with the use of the mApp (part 2, seven items). Questions on motherfit group therapy were, e.g. on whether the participant liked training in a group and if there were enough opportunities to ask the motherfit group therapist questions. Questions regarding satisfaction of the mApp were, e.g. on ease of use and whether participants would continue using the mApp after the intervention period. Each item ranges from 1 (strongly disagree) to 5 (strongly agree).

## Statistical methods

### Sample size calculation

Assuming that the average score of the primary outcome measure (ICIQ-UI-SF; range 0–21) of MOTHERFIT1 will lie at 8 and for MOTHERFIT2 at 9 (which is also the expected mean ICIQ-UI-SF score at 18 months post-partum in the CAU group; in contrast, the expected mean ICIQ-UI-SF score at 18 months post-partum in the experimental group is 5 (for MOTHERFIT1 and MOTHERFIT2) together with a relatively high standard deviation of 5 at baseline (because of the non-normality of the measure), participants will – with 97.5% probability – vary at baseline within the ranges of 0 to 19. The minimum acceptable score of participants to be treated is set at 3, so the range lies approximately between 3 and 19. From earlier studies [44], it became clear that the success of the PFMT exercises will be considerable and will be clinically relevant if the gain is higher than half the standard deviation of the baseline, presumably 3 with a somewhat smaller standard deviation of 3, because of the homogenising effects in the experimental arm. In contrast to MOTHERFIT1 (women remain stable), in MOTHERFIT2 it is assumed that the condition of CAU participants at 18 months will worsen with an average ICIQ-UI-SF score going from 9 in the baseline to 10 (SD 5).

Assuming two-sided testing, a power of 90% (beta = 0.10) and a significance level of 0.95 (alpha = 0.05) in each arm of the trial in MOTHERFIT1, minimally 60, and in MOTHERFIT2, minimally 35 participants will have to be included without taking into account that participants may drop out of the study during the 18 months of observations. Using a 20% dropout, in MOTHERFIT1 each arm will need 75 participants, 150 in total, and in MOTHERFIT2 each arm will need 45 participants, 90 in total.

### Statistical analysis

Analysis of the participants will be reported in accordance with the Consolidated Standards of Reporting Trials (CONSORT) Statement [44]. Data will be analysed according to the intention-to-treat principle. By preference, multiple-imputation techniques are used for missing values.

### Descriptive analysis

Firstly, descriptive, univariate statistics will be reported. In case of metric, normally distributed variables, mean and standard deviations are presented. If not normally distributed, medians and percentiles are presented. The Shapiro-Wilk test will be used to assess normality.

Process and structure indicators will be analysed with descriptive statistics and presented as absolute and proportion data (%) whenever the variable is categorical, or as mean (± standard deviation; 95% confidence intervals) or quartiles for continuous variables. A *p* value < 0.05 will be considered to be statistically significant. Data analysis will be carried out using SPSS version 25 (IBM. Corporation, Somers. NY, USA).

### Analysis of main hypotheses

In both studies, the main hypothesis concerns differential changes in ICIQ-UI-SF within time between two randomised groups of participants. (Repeated measurements) analysis of covariance (ANCOVA) will be performed with baseline measurements (T0) as covariate. Transformations of original scores will be attempted if the ICIQ-UI-SF shows a non-normal distribution at T0. Randomisation groups (motherfit group therapy versus CAU) are regarded as a between factor. Next, the within-participants linear trend in time of the outcome will be calculated with the weights from the first orthogonal polynomial contrast and this is used as a dependent variable in a multiple (dummy-)regression analysis. It concerns repeated measurements from T0 to T4 (MOTHERFIT1) and T0 to T3 (MOTHERFIT2). Next to the baseline covariate measurement and the randomisation groups’ dummy variable, other possible confounding variables will be used in this multiple linear regression analysis of the linear trend in time of the ICIQ-UI-SF.

The following potential confounding variables are considered to be used in the multiple linear regression analysis: Body Mass Index (BMI) before pregnancy (> 25), parity, maternal age (> 35 years) and the ability to perform a PFM contraction at baseline.

Forward selection and backward elimination techniques will be used to determine the best fit of the data to a final regression model. Testing of interactive relationships between statistically significant effects of predictors in the final model will be done, especially if it concerns the experimental between-randomisation groups’ factor. Listwise deletion of missing cases will be used in all linear regression modelling. This may be in case of loss-to-follow-up because of a succeeding pregnancy during the follow-up period of 18 months. For the final best-fitting regression model, a residual analysis will be done on the standardised Studentised z-scores and a screening will be performed on outliers to ensure the legitimacy and validity of the use of parametric statistics in analysis by testing the normality of distribution of the linear trend in ICIQ-UI-SF.

Statistical analysis on the secondary outcomes of the study, such as the IIQ-7, the GPE and the EQ-5D-5 L will be handled in the same way as the primary outcome measure ICIQ-UI-SF. Process and structure indicators will be analysed with descriptive statistics and presented quantitatively as numbers and absolute and proportion data.

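### No analysis named for the main hypothesis compares the arms at 18 months, and the linear-trend regression subtracts benefit seen at the first follow-up visit

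*Protocol article*

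**What the plan says.** The target is 18 months in three places of the Protocol article. In *Background*, the primary objective is to reduce, at that time, "post-partum UI severity (frequency, amount and impact) compared to CAU". In *Primary outcome measure*, therapy success (no UI, or at least 3 points of change) is judged at 18 months. In *Sample size calculation*, "the expected mean ICIQ-UI-SF score at 18 months post-partum in the experimental group is 5", set against 8 under care-as-usual in MOTHERFIT1 and 9 in MOTHERFIT2.

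The section *Analysis of main hypotheses* is framed differently: "the main hypothesis concerns differential changes in ICIQ-UI-SF within time between two randomised groups of participants". Two steps follow. First, a (repeated measurements) "analysis of covariance (ANCOVA) will be performed with baseline measurements (T0) as covariate", with arm as between factor and no time point given. Second, "the within-participants linear trend in time of the outcome will be calculated with the weights from the first orthogonal polynomial contrast", and that score becomes the dependent variable of a multiple regression on arm, baseline and possible confounders. On the visits used: "It concerns repeated measurements from T0 to T4 (MOTHERFIT1) and T0 to T3 (MOTHERFIT2"). The model selection, interaction tests and residual checks that follow belong to this regression.

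The visits are unequally spaced. For MOTHERFIT1, "data will be collected at baseline, 34 weeks of gestation, 6 weeks and 6 and 18 months post-partum"; for MOTHERFIT2, "data will be collected at baseline and 4, 9 and 18 months post-partum".

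**The concern.** A linear contrast measures how fast the arms separate over the visits. The trial asks how far apart they are at the last one. The two agree only for particular time courses. Women can start motherfit as soon as they are randomised (*Motherfit group therapy*), so benefit may already show at T1, where the contrast weight is negative. An ANCOVA averaged over follow-up visits errs the other way, because it credits benefit that has gone by 18 months. Since the article does not say which step decides, the same data could support different conclusions, and neither step as described isolates the quantity that the trial was sized for.

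**Working it through.** **1. The plan's own figure.** For two means, n per arm = 2(1.960 + 1.282)² × SD² / difference².
- MOTHERFIT1 (8 vs 5, SD 5): 2 × 10.507 × 25 / 9 = 58.4, so 59; 60 with the t distribution. Stated: 60. With 20% dropout, 60/0.8 = 75, as stated.
- MOTHERFIT2 (9 vs 5, SD 5): 2 × 10.507 × 25 / 16 = 32.8, so 33; 34 with t. Stated: 35. Then 35/0.8 = 43.75, so 44. Stated: 45.

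The stated sizes are those of a comparison of 18-month means, exactly in MOTHERFIT1 and closely in MOTHERFIT2.

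**2. Weights in the treatment effect.** First orthogonal polynomial, equal spacing: -2, -1, 0, 1, 2 for five visits and -3, -1, 1, 3 for four. T0 is also a regressor, so its coefficient absorbs the T0 term. The arm coefficient then estimates the sum of w × d over post-baseline visits, where d is the arm difference at each visit. The remaining weights are -1, 0, 1, 2 and -1, 1, 3.

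**3. What the contrast scores in MOTHERFIT1.** A negative score favours motherfit. The courses are illustrations; the article gives none.

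| Benefit at T1, T2, T3, T4 (points) | Contrast | True 18-month benefit |
|---|---|---|
| 3, 3, 3, 3 | 3 + 0 - 3 - 6 = -6 | 3 |
| 0, 0, 0, 3 | -6 | 3 |
| 0, 3, 3, 3 | 0 + 0 - 3 - 6 = -9 | 3 |
| 1, 2, 3, 3 | 1 + 0 - 3 - 6 = -8 | 3 |
| 6, 5, 4, 3 | 6 + 0 - 4 - 6 = -4 | 3 |
| 0, 3, 3, 0 | 0 + 0 - 3 + 0 = -3 | 0 |
| 3, 3, 3, 0 | 3 + 0 - 3 + 0 = 0 | 0 |
| 3, 3, 1.5, 0 | 3 + 0 - 1.5 + 0 = +1.5 | 0 |

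The first five courses have the same 18-month effect and scores from -4 to -9. The last three have no 18-month effect and scores from -3 to +1.5.

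**4. Power in MOTHERFIT1.** Inputs from the article: SD 5, 60 per arm, two-sided 5%. Assumption: exchangeable correlation ρ. The variance of the contrast given T0 is SD² × [(1-ρ)Σw² + ρ(1-ρ)(Σw)²], and SE = √(2 × variance / 60). Powers use the normal approximation; for the results listed here, t-based values agree within about one percentage point. At ρ = 0.5:
- Equal weights (Σw² = 6, Σw = 2): variance 25 × (3 + 1) = 100, SE 1.826. Sustained benefit: 6/1.826 = 3.29, power 91%.
- Real-time weights (T0 assumed at 20 weeks, delivery at 40, so weeks 20, 34, 46, 66, 118): centred, -36.8, -22.8, -10.8, 9.2, 61.2. Contrast 3 × 36.8 = 110.4, variance 64,296, SE 46.3, ratio 2.38, power 66%.
- T0-adjusted 18-month score alone: variance 25 × 0.75 = 18.75, SE 0.791, ratio 3.79, power 97%.

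At ρ = 0.3 / 0.5 / 0.7, sustained 3-point benefit: equal weights 83 / 91 / 98%; real-time weights 54 / 66 / 85%; 18-month test 93 / 97 / 99.6%.

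Other courses at ρ = 0.5, equal weights: 6, 5, 4, 3 gives 59%; 1, 2, 3, 3 gives 99%; 0, 3, 3, 3 gives 99.9%. The 18-month test stays at 97% for all three. For 3, 3, 1.5, 0, the trend is significant against motherfit in about 13% of trials (47% with real-time weights).

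**5. An ANCOVA averaged over T1 to T4.** Course 3, 3, 1.5, 0: mean benefit 7.5/4 = 1.875, variance 25 × (0.125 + 0.25) = 9.375, SE 0.559, ratio 3.35. About 92% of trials would be positive with no 18-month difference.

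**6. MOTHERFIT2** (35 per arm, sustained 4 points, ρ = 0.5). Equal weights: 12/3.327 = 3.61, power 95%. Real-time weights (months 1.5, 4, 9, 18): 26.5/9.90 = 2.68, power 76%. 18-month test: 4/1.035 = 3.86, power 97%.

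**The case against.** The strongest reply is that the trend regression is not declared to be the deciding test. The ANCOVA comes first, and an average group effect from it would credit early benefit; an analysis plan not shown here may settle the order. That stands, and it confines the sign problem to the second step. It does not supply an 18-month comparison. The article itself fixes the dependent variable, its weights and its visits, so the mismatch with its own endpoint is not just an omitted detail.

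It is also fair that the loss depends on the course. Strength training is prescribed for at least 5 to 6 months, and T1 can fall only 7 weeks after a baseline at 27 weeks' gestation, so benefit may build up. The equal-weight trend then has more power than the 18-month test. With equal weights and sustained benefit, power is close to the planned 90%. The large losses need real-time weights or an early peak, and the article does not say which spacing applies.

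Three stronger readings are tempting and not supported:
- A reader might infer that a faded benefit is always reported as harm. It is not: 3, 3, 3, 0 scores zero with equal weights, and 0, 3, 3, 0 scores in favour of motherfit.
- A reader might infer that T0 is an outcome in the ANCOVA as well as its covariate. The sentence listing T0 to T4 follows the trend sentence, so this is only one possible reading.
- A reader might infer that a curved course through pregnancy and delivery invalidates a linear contrast. A course common to both arms cancels in a randomised comparison.

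**Conclusion.** The point holds in this limited form: the article targets 18 months, names no 18-month comparison, leaves open which of two analyses decides, and defines one of them so that T1 benefit counts against motherfit. The weights and signs are exact for equal spacing and need no correlation assumption. With real-time weights T1 stays negative in both trials, and T2 becomes negative in MOTHERFIT1. A sustained benefit is not reversed. In MOTHERFIT1 at correlation 0.5 its power is about 91% (equal) or 66% (real-time), against about 97% for the direct test. The power figures rest on the assumed correlation, a common SD of 5, full follow-up of 60 (or 35) per arm, the assumed baseline week and the chosen course. The stated 90% power cannot be carried over to the trend.

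**What to change.** Name one primary analysis in each trial: the between-arm difference in ICIQ-UI-SF at 18 months post-partum, adjusted for T0, with its 95% confidence interval. Either an ANCOVA of the 18-month score or a repeated-measures model will do. The model would use post-baseline visits only, with visit as a category and arm-by-visit terms, and the 18-month contrast would be read off. Label the linear-trend regression exploratory and, if it is kept, state whether its weights follow visit order or real time.

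The data and sample size do not change: 60 and 35 completers per arm give about 93% power or more for this test at correlations from 0.3 to 0.7. *Trial status* reports recruitment under way, so the cost is a documented, dated amendment before any unblinded analysis. If benefit does build up steadily, the change also gives up the slightly higher power of the trend.
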